### Implementation {16c}

The GMP pharmacist is not involved in any other aspect of the study and will randomize the study medication in blocks of 6 with a randomization list generated with the Excel software programme. This will result in a balanced distribution of the labels A, B and C to the tubes with phenytoin 10%, 20% and placebo cream. The research physician will enrol the patients after performing DOBRET. The UMCU pharmacist will evaluate the outcome of the DOBRET, will stratify to DOBRET positive and DOBRET negative participants, and will randomly assign the participant to a study medication sequence (total of 6 possibilities, i.e. ABC, ACB, BAC, BCA, CAB, CBA) using a predefined randomization list.

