### Trial design {8}

This is a 6-week single-centre, enriched enrollment randomized double-blind, placebo-controlled triple cross-over trial to evaluate the efficacy and safety of phenytoin cream (20% and 10%) versus placebo in 48 participants with painful CIAP. The enriched enrollment is based on a positive double-blind placebo-controlled response test (DOBRET) in 48 participants who experience within 30 minutes at least 2 points pain reduction on the 11-point numerical rating scale (NRS) on the phenytoin 10% cream applied area and at least 1 point difference in pain reduction on the NRS between phenytoin 10% and placebo cream applied area, in favour of the former. To explore to which extent and which responder definition for the DOBRET has a predictive value for sustained pain relief, an additional 24 DOBRET negative participants will be included.

Participants will be randomly allocated to one of the 6 possible intervention sequences. Participants and investigators will be blinded. The duration of each treatment period is 2 weeks. Participants will cross-over two times to each of the other treatments. The study does not have wash-out periods between treatments, because the mean duration of the analgesic effect after an application is expected to be less than 9 h [19]. A flow chart of the study is presented in Fig. 1.

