### Intervention description {11a}

All participants will receive placebo, phenytoin 10% and phenytoin 20% cream, each during a period of 2 weeks. The participant will be instructed to apply the cream 2 to 4 times a day with a maximum of 1.5 g per application, measured in Finger Tip Units (FTU).

One FTU is defined as the amount of cream expressed from a tube with a 5 mm diameter nozzle, applied from the distal skin crease to the tip of the index finger, which amounts to approximately 0.5 g (see Fig. 2). The number of daily applications depends on the duration of the analgesic effect and the amount of cream depends on the size of the painful areas, e.g. both feet 1 FTU, and both feet and lower legs 3 FTU. The participant can apply the cream with bare hands, and then wash the hands after each application. After the double-blind period participants are invited to use phenytoin 20% cream in the 1-year open-label extension phase, to study the long-term pain reduction and safety.

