#### Secondary outcomes

All secondary outcomes are evaluated for phenytoin 20% versus 10% versus placebo cream in DOBRET positive, negative and all participants.

The change between baseline and week 2 for each intervention is assessed for:Pain intensity measured on theNRSNeuropathic Pain Symptom Inventory (NPSI), evaluating on the NRS neuropathic pain characteristics [27]NRS for the 3 worst pain characteristics≥30% and ≥50% improvement on the NRS compared to placebo within one participant, reflecting at least moderate and at least substantial improvement [28]Patient-reported percentage of pain reduction at the end of the second week of each interventionOnset of the analgesic effect after applicationDuration of the analgesic effect after one applicationDaily number of cream applicationsUse of escape pain medicationQuality of life measured on thesubscales of the Brief Pain Inventory (sBPI), evaluating on the NRS pain interference regarding general activity, mood, walking ability, normal work, relations with other people, sleep, and enjoyment of life [29]EQ5-5D-5L, measuring the health status on the visual analogue scale, and on a 5-point scale pain/discomfort, anxiety/depression, mobility, self-care and usual activities [30]Patient Global Impression of Change Scale (PGIC), measured on a 7-point scale [31]To evaluate the safety and tolerability of phenytoin 10% and 20% creamTolerability is defined as time-to-discontinuation of an assigned treatment since randomization.Safety is based on the safety assessments including physical examinations, clinical laboratory evaluations, vital signs and frequency of AEs or SAEs. (S)AEs will be categorized according to the Common Terminology Criteria for Adverse Events and will be rated for severity and association with the study drug.Detection of phenytoin in plasmaPredictive value of DOBRET in sustained pain reduction due to phenytoin creamTo evaluate the correlation between the PCS and the pain-reducing effect of topical phenytoin

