### Sample size {14}

We hypothesized a mean difference of 2 points on the NRS between placebo and the 20% cream (π1), and a mean difference of 1 point between 20% and 10% cream (π2). Based on preliminary data [21], we assumed for both treatment effects a standard deviation of 3.3 (standardized effect sizes: π1 = 0.61, π2 = 0.30). Using the same dataset, we conservatively assumed a correlation between NRS scores within participants (intraclass correlation) of 0.3. Seven participants per sequence (e.g. placebo–20%–10%, or 10%–placebo–20%) would be required to achieve 80% power and a two-sided significance level of 5% (= 7 × 6 sequences = 42 total sample size) [32]. Assuming a 10% drop-out rate, we will enrol 8 responding participants per group or 48 in total. DOBRET-negative participants are assumed to exhibit a mean difference of 1.5 point s (SD 4) on the NRS between placebo and the 20% cream, where 1 in 3 patients are assumed to be DOBRET-negative. This would result in a pooled overall treatment effect across DOBRET negative and positive participants of 1.83 (SD 4). Enrolling 24 DOBRET-negative and 48 DOBRET-positive participants would result in a power of 84% for the overall population.

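### Tolerability is timed from the single randomisation to a three-cream sequence, so a cream used in period 2 or 3 is credited with 14 or 28 days spent on other creams

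*Protocol article*

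**What the plan says.** Secondary outcomes lists tolerability among the safety items. It is the time until an assigned treatment is discontinued, with randomisation as the starting point. The same section sets the level of comparison: "All secondary outcomes are evaluated for phenytoin 20% versus 10% versus placebo cream in DOBRET positive, negative and all participants".

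The rest of the protocol describes one randomisation per participant, to an order of creams:

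- Trial design {8}: "Participants will be randomly allocated to one of the 6 possible intervention sequences".
- Implementation {16c}: the pharmacist "will randomly assign the participant to a study medication sequence (total of 6 possibilities, i.e. ABC, ACB, BAC, BCA, CAB, CBA".
- Intervention description {11a}: "All participants will receive placebo, phenytoin 10% and phenytoin 20% cream, each during a period of 2 weeks".
- Trial design {8}, on timing: "The duration of each treatment period is 2 weeks", and "The study does not have wash-out periods between treatments".

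Nothing in the article re-randomises a participant at the start of a period or restarts the tolerability clock there.

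**The concern.** A clock that starts at randomisation suits a parallel-group trial, where randomisation and the start of treatment nearly coincide. Here they coincide only for the cream used first. For the second and third creams, the recorded time includes 14 or 28 days during which that cream could not be stopped because it had not been started.

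Neither reading of assigned treatment removes the problem. If it means the cream, the origin is wrong in periods 2 and 3. If it means the whole sequence, the clock is coherent, but the outcome can no longer be compared between creams as the section requires. The definition also leaves open how to count creams that were assigned but never started because the participant left earlier.

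At stake is the description of how long each cream is tolerated. The recorded time would partly describe the order drawn.

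**Working it through.** The protocol gives no figure for tolerability, so there is nothing to reproduce.

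**Inputs from the protocol.** Six sequences of three creams, 14-day periods, no wash-out (Trial design {8}, Implementation {16c}); 48 + 24 = 72 participants; a 10% drop-out rate (Sample size {14}).

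**Assumptions.** The 14-day risk of stopping a cream, p, is 3% to 10%, with stops spread evenly over the 14 days. For context, if the 10% drop-out covers all six weeks and is spread evenly, p = 1 − 0.9^(1/3) ≈ 3.5%.

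**1. Start days.** The cream in period k starts on day 14 × (k − 1), that is day 0, 14 or 28. The last period ends on day 42, which agrees with the stated six weeks.

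**2. Recorded times.** Recorded time = 14 × (k − 1) + days on the cream.
- A stop after 3 days: 3, 17 or 31.
- A completed period: 14, 28 or 42, mean 28 instead of 14.

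**3. Balance.** Over the six sequences, each label starts twice on day 0, twice on day 14 and twice on day 28. The mean offset is 14 days for every cream.

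**4. Person-time rates.** Mean days on the cream's own clock = 14(1 − p) + 7p = 14 − 7p. On the randomisation clock, add 14.

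| p | Own clock: days; stops per 100 days | Since randomisation: days; stops per 100 days | Ratio of rates |
|---|---|---|---|
| 3% | 13.79; 0.218 | 27.79; 0.108 | 0.50 |
| 6% | 13.58; 0.442 | 27.58; 0.218 | 0.49 |
| 10% | 13.30; 0.752 | 27.30; 0.366 | 0.49 |

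A simulation with constant hazards, in which a participant who stops a cream leaves the trial, gave the same picture. True rates of 0.218, 0.442 and 0.753 became 0.112, 0.220 and 0.373. The ratio between the 10% and 3% creams barely moved: 0.753/0.218 = 3.45 true, against 0.373/0.112 = 3.33.

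**5. Discontinuation curve.** Assume all participants start every cream and each cream is used equally often in each period.
- Crude cumulative proportion at days 14, 28 and 42: p/3, 2p/3 and p.
- Kaplan–Meier, censoring each completed period at its end: the three 14-day steps have risks p/3, p/2 and p, because the risk set falls from all exposures to two thirds and then one third.

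| p | Crude: day 14, 28, 42 | Kaplan–Meier: day 14, 28, 42 |
|---|---|---|
| 3% | 1.0%, 2.0%, 3.0% | 1.0%, 2.5%, 5.4% |
| 10% | 3.3%, 6.7%, 10.0% | 3.3%, 8.2%, 17.4% |

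For p = 10%, the day-42 value is 1 − 0.9667 × 0.95 × 0.90 = 17.4%. Neither curve shows the true p at 14 days.

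**6. Noise among those who stop.** Variance of the offsets = (14² + 0 + 14²)/3 = 130.7 (SD 11.4 days). Variance of a uniform stop time = 14²/12 = 16.3 (SD 4.0 days). Position accounts for 130.7/147.0 = 89% of the variance in recorded stop times. With 72 × 0.10 = 7.2 stops per cream, a difference in mean stop time between two creams has a standard error from position of √(2 × 130.7/7.2) ≈ 6 days, against √(2 × 16.3/7.2) ≈ 2 days from real variation. With 72 × 0.03 = 2.2 stops per cream, these become about 11 and 4 days.

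**The case against.** The strongest reply is that the article sets no estimator, censoring rule or test for tolerability, and that these may properly be left to an analysis plan. Days spent on other creams do harm only if counted as time at risk. An analyst could keep randomisation as the time scale and let each cream enter the risk set on day 14 or 28, or simply count stops per cream. Period starts are fixed by design, so time on each cream can be recovered and no data are lost. This is fair as far as it goes. But the point concerns the time origin, which the protocol does state. Delayed entry or simple counts would be sensible departures from that definition, not applications of it.

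Three stronger readings are tempting, and the documents do not support them.

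- *The comparison between creams is biased.* A reader might infer this from the 14- and 28-day offsets. With balanced sequences the offset averages 14 days for every cream, and the ratio is roughly kept. Balance is not exact, since someone who leaves early never reaches the later creams, but the simulated shift was small (3.45 to 3.33).
- *Discontinuation is understated throughout.* This holds for the person-time rate and for day 14 of the curve. With completed periods censored, the curve exceeds the true 14-day risk by day 42.
- *The primary safety objective is compromised.* Objectives {7} bases safety on reported side effects and plasma levels and does not name tolerability, which appears only as a secondary outcome.

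**Conclusion.** The point holds in a limited form. As defined, tolerability does not measure time on a cream in periods 2 and 3: it is too long by 14 or 28 days. Period 1 times are right. Person-time rates come out at about half their true value over the assumed range of 3% to 10%, and recorded stop times are dominated by period position. These sizes rest on assumed risks, even spacing of stops and equal use of the three positions; the 14- and 28-day offsets rest on the design alone. The primary outcome, the sample size and the mixed model are unaffected. With perhaps two to seven stops per cream, counts will carry most of the information, and the clock does not alter them. It is still a stated rule that gives wrong per-cream times, and it is best settled before unblinding so that the choice of clock is not made after seeing the results.

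**What to change.** Under Secondary outcomes, define tolerability per cream as the time from first application of that cream in its own period to stopping that cream, censored at the end of that 2-week period. State that a stop is charged only to the cream in use, so creams never started contribute nothing, and that the comparison between creams accounts for period. Because few stops are expected, also report the number of participants stopping each cream. A within-participant Cox model is not required.

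The cost is a sentence or two in one outcome definition. Daily applications are already entered in the diary and visits are every two weeks (Strategies to improve adherence {11c}), so the dates should already exist. No patients, visits or measurements are added.

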## Assignment of interventions: blinding

### Who will be blinded {17a}

Participants, investigators, site personnel, and the study statistician are masked to treatment allocation. All randomized participants who received at least one dose of the study drug will be included in the analysis.

### Procedure for unblinding if needed {17b}

Only the UMCU pharmacist can unblind the creams in case of emergency. Unblinding can be performed 24 h a day.

## Data collection and management

### Plans for assessment and collection of outcomes {18a}

Demographic data and baseline assessments will be collected through an electronic or paper questionnaire. Medical history and past and current analgesic use with its effects will be asked at baseline visit or extracted from the UMCU electronic medical records. At baseline, at the 14th day of each treatment period, 3, 6 and 12 months of the open-label extension self-administered questionnaires will be collected (see for types of questionnaires Table 1). In the 6-week double-blind period, the NRS and the use of escape medication will be queried every evening. Adverse events will be asked and registered at each visit after a treatment period, and in the questionnaires in the open-label extension at 3, 6 and 12 months. The electronic questionnaires are automatically locked after completion. Research physician will enter the paper questionnaires into the electronic system and will store the paper questionnaires for 15 years. After completion of the trial and filling in all paper questionnaires, the electronic database will be locked. The analysis of phenytoin plasma levels will be performed with state-of-the-art liquid chromatography–mass spectrometry.

### Plans to promote participant retention and complete follow-up {18b}

Participants will be seen at the 14th day at every treatment period in the double-blind phase. Electronic pain diaries are stimulated to use over paper pain diaries and can be monitored continuously, and reminders will be sent electronically or will be given by phone when necessary. At 3, 6, and 12 months in the open-label extension phase, questionnaires will be sent electronically or on paper by post with a return envelope.

### Data management {19}

Pain diaries, questionnaires and research physicians’ case report forms will be directly stored in Castor, on a European server. Castor is an electronic data capture system for medical research [33]. Paper diaries and questionnaires will be securely 15 years stored in UMCU and entered into Castor by the research physicians.

### Confidentiality {27}

All participant data are stored pseudonymously. The participant coding list will be stored on a secured server and only research physicians, principal investigator, UMCU pharmacist, and independent auditor will have access. Informed consent forms, paper pain diaries and questionnaires will be stored in a locked closet, which can only be accessed by the principal investigator and research physicians. Participant information will be kept confidential.

### Plans for collection, laboratory evaluation and storage of biological specimens for genetic or molecular analysis in this trial/future use {33}

Blood samples will be collected in 1 ethylenediaminetetraacetic acid (EDTA) tube to measure free phenytoin (10%) and bound phenytoin (90%) in plasma. The specimen label will contain the participant study number. Blood samples will be stored at the UMCU laboratory, until the study is completed. The batch of blood samples from patients who were randomized during the first treatment period in the groups phenytoin 10% and 20% cream will be analysed to determine phenytoin plasma concentration. Unblinding of laboratory staff for treatment allocation will be done by the UMCU pharmacist. All samples will be destroyed after testing.

## Statistical methods

### Statistical methods for primary and secondary outcomes {20a}

Descriptive statistics will be used for baseline characteristics/demographics (age, sex, highest degree of education, country of birth, profession, duration and localization of pain, current neuropathic pain therapy, and past analgesic use), use of study creams (daily amount of use, number of daily applications, onset, duration and percentage of analgesic effect).

The primary endpoint measured on the NRS, as well as all other secondary endpoints, will be analysed according to the intention-to-treat (ITT) principle, incorporating all participants randomized irrespective of receiving treatment and having at least one efficacy measurement. For the primary analysis, the treatment effect will be determined in participants with a DOBRET-positive response at screening, evaluating the mean difference in NRS at week 2 between placebo and phenytoin 20% cream. Linear mixed-effects models (LME) will be used to account for the intra-individual clustering of observations. In brief, we will use an LME with fixed effects for time (week 1 or 2), treatment period (1 or 2 or 3), treatment (20% or 10% or placebo), the interaction between time and treatment, and NRS score at screening. The random part will be modelled with a random intercept and slope for time per individual, and an unstructured covariance matrix. The random slope for time will be kept in the model only if statistically significant. The likelihood ratio test will be used to test the significance of treatment; 95% confidence intervals will be based on the profile likelihood. Sensitivity analyses will be performed to evaluate (1) treatment-period interaction to assess potential carry-over effects and (2) per-protocol analysis involving all participants who completed the study. As secondary analysis, we will evaluate the treatment effect in all randomized patients irrespective of DOBRET, and explore the interaction between DOBRET outcome and treatment using additional interaction terms. Treatment effects on the NPSI, EQ-5D-5L, sBPI and PGIC will be evaluated in the same manner as the primary outcome.

Furthermore, the number of participants with a minimal pain relief (MPR), defined as the minimal percentage of pain reduction in the 7-day average pain intensity, as measured by the NRS, over week 2, will be calculated, for phenytoin 10%, phenytoin 20% and placebo cream. The number of participants experiencing the following MPRs will be determined:MPR30, at least 30% improvement as moderate pain improvementMPR50, at least 50% improvement as substantial pain improvement

Regression analyses will be performed to explore associations between DOBRET results and pain reduction during the intervention periods.

The statistical analysis will be performed with SPSS 22 (SPSS Inc., Chicago, IL, USA) and with the R-project, www.R-project.org (R Development Core Team (2008). R: A language and environment for statistical computing. R Foundation for Statistical Computing, Vienna, Austria. ISBN 3-900051-07-0).

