### Strategies to improve adherence to interventions {11c}

Participants can choose to fill in the pain diary and questionnaires electronically or on paper. Participants fill in every day the pain diary to score daily pain intensity on the NRS, number of daily cream applications and possibly used escape medication. Questionnaires are filled in only at the last day of each 14-day intervention period. When the pain diary is not filled in, the electronic questionnaire system Castor will send reminders the next day in the morning and the day after. Every 2 weeks the participant will visit the outpatient clinic to receive the study medication. The research physician checks at every visit the pain diary and questionnaires for completion.

In case the questionnaires are not filled in on the 14th day, the research physician will ask the participant to fill in the questionnaire at the visit on the 15th day.

When the pain diary is incomplete at the first visit, the research physician will stipulate the importance of filling in the pain diary and will monitor in Castor thereafter every day. In case the pain diary is not filled in, the patient will be phoned to ask the pain intensity on the NRS of the previous day, which will be noted, and will resolve the problem of poor adherence. When after the first 2 weeks less than 2 daily cream applications have been entered in the pain diary, the participant will be reinstructed during the second visit. The research physician will then monitor in Castor every day, and patients will be contacted in case of poor adherence. When poor adherence on paper diary and questionnaires is noticed in the first visit, daily phone calls will be performed in the second and third intervention periods. The outcomes will be registered in Castor and compared with the paper version. In case the participant experiences adverse events, one of the research physicians can be contacted for advice. Participants can contact the neurology department 24 h a day.

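### The primary mixed model has no participant-by-period term, so the week-2 treatment test is modestly anti-conservative if weeks on the same cream are more alike than weeks in different periods, and the likelihood ratio test is not tied to that contrast

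*Protocol article*

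**What the plan says.** All places are in the Protocol article. Under Statistical methods for primary and secondary outcomes {20a}, the target is fixed as "evaluating the mean difference in NRS at week 2 between placebo and phenytoin 20% cream". The fixed part contains week, period, treatment, "the interaction between time and treatment, and NRS score at screening". For the random part: "The random part will be modelled with a random intercept and slope for time per individual, and an unstructured covariance matrix". Then: "The random slope for time will be kept in the model only if statistically significant". For testing: "The likelihood ratio test will be used to test the significance of treatment". The terms removed for that test and its degrees of freedom are not given.

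The same section adds: "Treatment effects on the NPSI, EQ-5D-5L, sBPI and PGIC will be evaluated in the same manner as the primary outcome". Strategies to improve adherence to interventions {11c} says of these instruments: "Questionnaires are filled in only at the last day of each 14-day intervention period".

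**The concern.** Each participant supplies six weekly means, two in each of three periods. Under the stated random part with the slope dropped, two weeks on the same cream are assumed to be no more alike than two weeks in different periods on different creams. In a cross-over, treatment is compared between periods within a participant, so variation of the participant's level from period to period belongs in the error for treatment. The trial's own rationale makes such variation likely. It expects participants to differ in their response to phenytoin, and a personal response to a cream is shared by both weeks of the period in which it is used. If this component exists and is left out, standard errors are too small and the nominal 5% level is not held.

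A second, smaller problem needs no assumption. The questionnaires yield one value per period, so the week effect, the week-by-treatment interaction and the slope for week cannot be estimated for them.

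**Working it through.** **Inputs.** From Sample size {14}: SD 3.3, within-participant correlation 0.3, differences of 2 points (20% versus placebo) and 1 point (20% versus 10%), 7 × 6 = 42 participants, 48 after allowing for drop-out, two-sided 5%. Not in the document: the correlation r between weeks 1 and 2 of one period. It is varied below.

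**1. The plan's own figure.** With one value per period and a 2-df within-participant F test, the noncentrality is n × Σ(μ − mean)² / [SD² × (1 − 0.3)]. Means 0/1/2 give Σ = 2, and 10.89 × 0.7 = 7.623. For n = 42 this is 84/7.623 = 11.02, power 83.9%. For n = 36 it is 9.45, power 77.2%. So 42 is the smallest multiple of 6 that reaches 80%. The sample size rests on one value per period and is not affected by this point.

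**2. Variance components.** Write a weekly value as participant + participant-by-period (variance sp²) + residual (variance se²). Let s = sp²/(sp² + se²). With between-period correlation 0.3, s = (r − 0.3)/0.7, so r = 0.6, 0.8, 0.9 gives s = 0.43, 0.71, 0.86, and r = 0.3 gives s = 0.

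**3. Slope dropped.** The six values leave 5 df within a participant. The expected residual mean square is (4sp² + 5se²)/5 = 0.8sp² + se².

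- *Week-2 contrast.* It needs sp² + se². The ratio of true to modelled variance is 1/(1 − 0.2s), at most 1.25. The standard error is too small by 1 − √(1 − 0.2s), which is 9.4% at s = 0.9 and 10.6% in the limit.
- *Week-averaged contrast.* The ratio is (1 + s)/(1 − 0.2s), at most 2.5.

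**4. Slope in the model.** Removing each participant's mean and week trend leaves 4 df, with expectation (4sp² + 4se²)/4 = sp² + se², which is what the week-2 contrast needs. This requires a slope variance estimated above zero. If sb² is the true slope variance, the week-trend mean square has expectation 1.5sb² + se². It exceeds sp² + se² only when 1.5sb² > sp². Otherwise the slope variance is estimated at zero and the fit returns to step 3.

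**5. Type I error for tests at nominal 5%.** Simulation: n = 42, 10,000 null trials per setting, maximum likelihood, the protocol's slope rule, no true slope variance. The screening covariate is left out because it does not affect within-participant contrasts.

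| s | 0.25 | 0.5 | 0.75 | 0.9 | 0.99 |
|---|---|---|---|---|---|
| Week 2, 20% v placebo, analytic | 5.6% | 6.3% | 7.1% | 7.6% | 7.9% |
| Week 2, 20% v placebo, simulated | 5.9% | 6.7% | 7.8% | 8.9% | 8.7% |
| Joint test of treatment and interaction, 4 df, simulated | 6.6% | 9.6% | 13.1% | 14.8% | 16.4% |
| Week-averaged treatment, 2 df, simulated | 10.6% | 17.7% | 25.3% | 29.3% | 32.9% |

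At s = 0 the simulated week-2 test runs at 5.4%, so a few tenths of a point come from the small-sample likelihood test itself. The slope was kept in under 1% of trials for s ≥ 0.25.

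**6. True slope variance present.** With slope variance equal to 0.75 of the within-participant variance, the slope was kept in 74–88% of trials (s = 0.25–0.99). The week-2 test then ran at 5.3–6.1%, the joint test at 5.9–10.7% and the week-averaged test at 9.7–24.7%.

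**7. Benchmark.** Week-2 values only, with participant, period and treatment, gave 4.6–5.2% in every setting.

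**The case against.** The strongest reply is that the primary quantity is a week-2 difference in a model with a week-by-treatment interaction. Week 1 is therefore not a replicate of week 2 and enters only through the residual variance. This is right, and it limits the damage. A reader might infer that the primary test runs far above 5%, at 15–30%. The document does not support that. Those rates need a test averaged over weeks, which the section does not specify and which would sit badly with its week-2 target. The 4-df joint reading is not specified either. What stands is that the test is described only as one of treatment, so neither reading is excluded.

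Second, the key input is assumed. No within-period correlation is given, and the between-period value of 0.3 is called conservative. With r = 0.8 and a between-period correlation of 0.6, s = 0.2/0.4 = 0.5 and the analytic rate is 6.3%, against about 7.0% at 0.3. This stands, and it is why a range is shown.

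Third, where participants differ strongly in their week trend, the slope is usually kept and the week-2 test is close to nominal (step 6). This also stands. It would be wrong, though, to infer that the slope rule is the root cause and that deleting it alone would suffice. By step 4, a slope with little true variance is estimated at zero and corrects nothing.

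Fourth, the unstructured matrix might mean the residual covariance of all six weekly values, in which case the concern would fail. That reading is unlikely. Such a matrix would already absorb the intercept and slope, and testing whether to keep the slope would have no purpose. The article introduces the model as a brief account, so the full protocol may be clearer, but the random part is stated and not merely omitted.

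Fifth, analysing questionnaires in the same manner may only mean by mixed model. That is a fair reading, and the matter is then one of wording.

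**Conclusion.** The concern holds in a limited form. As written, the model omits participant-by-period variance. For the week-2 contrast of 20% versus placebo this means a standard error up to about 10% too small and a type I error of about 6–8% analytically, 6–9% in simulation. These figures assume s between 0.25 and 0.99, the slope dropped and no true slope variance. At s = 0 the omission causes no inflation, and with large slope variance there is little. Because the likelihood ratio test is not defined, a joint test (about 7–16%) or a week-averaged test (about 11–33%) under the same assumptions is not ruled out. Those ranges describe possible readings, not the plan's stated primary contrast. The questionnaire point holds as a matter of wording and needs no assumption.

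**What to change.** Run the primary analysis on one value per participant and period, the week-2 7-day mean, with fixed treatment, period and screening NRS and a random participant intercept. Define the primary test as the 1-df contrast of 20% versus placebo. Use the same model for NPSI, EQ-5D-5L, sBPI and PGIC.

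If week 1 is kept, add a random intercept for participant-by-period, delete the keep-if-significant rule for the slope, and still name the 1-df week-2 contrast as the primary test.

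Cost: a change of wording, and slightly larger standard errors. Power for 2 points remains ample. The standard error of the difference is √(2 × 10.89 × 0.7/n), which is 0.602 at n = 42 and 0.564 at n = 48. So 2/SE is 3.32 and 3.55, and power is about 91% and 94%. The sample size need not change. A week-2-only analysis makes no use of a period with week-1 scores but no week-2 scores. If that matters, the version that keeps week 1 is preferable.
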